#### Analysis of the secondary outcomes

To evaluate robustness of the results a sensitivity analysis of the primary outcome will be done using different analysis sets.Analysis set without failures: patients that have a failure within the 6 months of follow-up are excluded from this analysisAnalysis set without re-surgeries: patients that have a re-surgery within the 6 months of follow-up are excluded from this analysisIn case we are not able to show superiority between the arms, we will consider non-inferiority between the arms. To this end we will choose 10 IKDC points as non-inferiority margin (see Hoogeslag et al. [25]). Non-inferiority will be considered in the different analysis sets and only be concluded if they give similar findings. The analysis sets considered here are intention-to-treat, the analysis set without failures and the analysis set without re-surgeries.As the IKDC scores are measured at many different time points during the patient’s follow-up we can compare the evolution over time between the treatment arms using a linear mixed model. Also here we will consider the effect of failure and re-surgery through inclusion and exclusion of the results after failure.Linear regression will be performed on the changes from baseline to 24 months in the continuous outcomes like VAS pain, VAS satisfaction, Tegner score, Lysholm score, EQ-5D-5 L, Lachman test, single leg and triple leg hop test, triple crossover hop and drop jump test, isokinetic and proprioceptive measurement and knee function. The evolution over time of these continuous outcomes will be compared between the different treatments using a linear mixed model.A survival analysis with log-rank test will be used to compare the time to return to work and time to return to sports between the different treatment arms. The time from the surgery until the patient is mobile without crutches will be analysed in the same way.The number of physiotherapy/orthopaedic surgeon consults will be compared between the different treatment arms using linear regression.The morphology and signal intensity of the ACL will be assessed with MRI and compared between the different treatments using a Chi-square test at the different time points.

In all the analyses there will be appropriately corrected for possible confounders (age, gender, working category, Tegner score of more than 7) especially in the analysis where the ACL reconstruction arm is compared to the DIS arm as this is a non-randomized comparison. As the sample size is small mainly ANCOVA models where only one covariate is added will be explored. As the sample size will not allow to combine all covariates in the model any conclusion for the non-randomized comparison will be carefully stated.

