### Study design

The **LIBRƎ** trial is a single-blind, multi-center, prospective, RCT comparing **L**igamys® anterior cruciate ligament (ACL) repair, ***I****nternal***B**race™ ACL repair and conventional ACL **re**construction for relative clinical efficacy and economic benefit.

Patients admitted for an acute traumatic knee sprain needing ACL surgery will be recruited at the Antwerp University Hospital and University Hospital Brussels, Belgium between February 2018 and June 2020.

The LIBRƎ study is single-blind, meaning that the patient and the physiotherapist are blinded to the performed surgical technique, but they are aware in which part of the study the patient participates (study 1 or study 2). Patient’s physiotherapist will follow a study-specific rehabilitation protocol (identical for the three treatment arms), depending on the readiness of the patient for a next phase and not restricted to a predefined time line.

In the study design, the time-dependent nature of ACL repair surgeries has been taken into account. The company Mathys Ltd. advices DIS to be performed within 3 weeks after the ACL rupture. Previous ACL repair surgery experience from the authors ([name]) led to a prolonged DIS ACL repair period within 4 weeks post-rupture. IBLA can be performed up to 12 weeks after the ACL rupture. ACL reconstruction is preferably performed when the knee has regained its function. This is commonly after 4 weeks post-rupture and can be performed up to many years later. Taken into account these time limits there will be two parallel studies (flowchart, Fig. 1):
Study 1 (RCT 1) with a time frame 0–4 weeks post-rupture: patients are randomized 1:1 to DIS or IBLAStudy 2 (RCT 2) with a time frame 5–12 weeks post-rupture: patients are randomized 1:1 to IBLA or conventional ACL reconstruction.

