### Study population

#### Inclusion criteria

Primary acute proximal ACL rupture: 3-digit ACL rupture classification, type A (MRI and intra-operative confirmation) [17] (Fig. 2).Age: 18–50 years.Presented and planned surgery within 4 weeks after the ACL rupture (Study 1).Presented and planned surgery between 5 and 12 weeks after the ACL rupture (Study 2).The ACL remnant is suitable for repair in the three treatment arms: at least 75% of the distal ACL remnant must be in contact with the proximal remnant/femoral condyle (intra-operative confirmation).Mentally and verbally capable of participating in the study.Written informed consent (according to the ICH-GCP Guidelines).

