### Study procedures

Table 1 gives an overview of the clinical and radiological evaluations the patient will encounter in both centers following written informed consent. The physiotherapy will be performed by the patient’s physiotherapist according to the study-specific rehabilitation protocol. This physiotherapy protocol is based on five phases. Proceeding to the next phase depends on the patients rehabilitation progress and not on the post-operative time.

**Table 1 Tab1:** Pre-, intra- and post-operative clinical and radiological evaluations

Timepoint	Clinical and radiological evaluations
Pre-operative	Pre-rupture: Tegner score, Lysholm score and IKDC score Post-rupture: VAS pain, knee function, Lachman test, EQ-5D-5 L, isokinetic and proprioceptive measurement, and MRI
Intra-operative	Knee function, pivot shift test, surgery time and complications
Post-Operative	
Day 1	VAS pain, return to work rupture-surgery interval, EQ-5D-5 L and complications
Week 2	VAS pain, return to work, knee function, EQ-5D-5 L and complications
Week 6	VAS pain and satisfaction, mobilization with crutches, return to work, return to sports, knee function, Lachman test, EQ-5D-5 L, complications and X-ray knee
Week 13 (3 months)	VAS pain and satisfaction, mobilization with crutches, return to work, return to sports, knee function, Lachman test, EQ-5D-5 L, Tegner score, Lysholm score, IKDC score, complications, and isokinetic and proprioceptive measurement
Week 26 (6 months)	VAS pain and satisfaction, return to work, return to sports, knee function, Lachman test, EQ-5D-5 L, Tegner score, Lysholm score, IKDC score, complications, number of physiotherapy and orthopaedic surgeon consults, single leg and triple leg hop test, isokinetic and proprioceptive measurement, and MRI
Week 52 (1 year)	VAS pain and satisfaction, return to work, return to sports, knee function, Lachman test, EQ-5D-5 L, Tegner score, Lysholm score, IKDC score, complications, number of physiotherapy and orthopaedic surgeon consults, single leg and triple leg hop test, triple crossover hop and drop jump test, isokinetic and proprioceptive measurement, and MRI
Week 104 (2 years)	VAS pain and satisfaction, return to work, return to sports, knee function, Lachman test, EQ-5D-5 L, Tegner score, Lysholm score, IKDC score, complications, number of physiotherapy and orthopaedic surgeon consults, and MRI

*IKDC* International Knee Documentation Committee, *MRI* magnetic resonance imaging, *VAS* visual analogue scale

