### Statistical analyses

#### Analysis of the primary outcome

To answer the research question comparing the three treatment arms the research question is split up in three separate questions:
*Is there a difference between DIS and IBLA (≤4 weeks)?*

Results from study 1 will be used in a linear regression model with IKDC at 6 months as outcome and treatment, and IKDC at baseline as predictors. This linear regression model will allow correction for possible confounders like age, gender and working category.
*Is there a difference between IBLA (5–12 weeks) and conventional ACL reconstruction?*

Results from study 2 will be used in a linear regression model with IKDC at 6 months as outcome and treatment, and IKDC at baseline as predictors. This linear regression model will allow correction for possible confounders like age, gender and working category.
*Is there a difference between DIS and conventional ACL reconstruction?*

Results from study 1 and study 2 will be compared using a linear regression model with IKDC at 6 months as outcome and treatment, and IKDC at baseline as predictors. As this is a non-randomized comparison this model will correct for possible confounders like age, gender and working category.

For the primary analysis all patients that didn’t have a repairable, proximal ACL rupture will be excluded from the analysis (exploratory group). Patients with a failure or re-surgery will be included in the primary analysis.

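### Continuous secondary outcomes are analysed as change to 24 months without the baseline as covariate: imprecise in both randomised comparisons, and open to bias for DIS versus reconstruction on the four outcomes with a post-rupture baseline

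*Protocol article*

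**What the plan says.** Under Analysis of the secondary outcomes the protocol states: "Linear regression will be performed on the changes from baseline to 24 months in the continuous outcomes like VAS pain, VAS satisfaction, Tegner score", and the list goes on to Lysholm, EQ-5D-5L, Lachman, the hop and drop-jump tests, the isokinetic and proprioceptive measures, and knee function. A linear mixed model over time is planned for the same outcomes. The closing paragraph of that section names age, gender, working category and a Tegner score above 7 as confounders, expects mostly ANCOVA models with one added covariate, and promises caution on the non-randomised comparison. Neither the outcome's own baseline nor time since rupture is on the list.

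The primary outcome is handled differently. Analysis of the primary outcome specifies a "linear regression model with IKDC at 6 months as outcome and treatment, and IKDC at baseline as predictors".

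Table 1 (Study procedures) gives two kinds of pre-operative value: "Pre-rupture: Tegner score, Lysholm score and IKDC score" and "Post-rupture: VAS pain, knee function, Lachman test, EQ-5D-5 L, isokinetic and proprioceptive measurement, and MRI". The week 104 row ends with "complications, number of physiotherapy and orthopaedic surgeon consults, and MRI" and lists no hop, drop-jump, isokinetic or proprioceptive test.

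Under Inclusion criteria, presentation and planned surgery fall within 4 weeks of rupture in study 1 (DIS, IBLA) and between 5 and 12 weeks in study 2 (IBLA, reconstruction). Study design adds that "ACL reconstruction is preferably performed when the knee has regained its function", which it places commonly after 4 weeks.

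**The concern.** Two separate things are at stake.

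The first is precision in the randomised comparisons. A change score subtracts the whole baseline whatever its correlation with the follow-up value. When that correlation is modest, the subtraction adds noise. The baseline is already collected and the protocol already uses the better model for IKDC, so with about 21 evaluable patients per arm the loss is avoidable.

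The second is bias in the non-randomised comparison. For four outcomes measured at both ends (VAS pain, knee function, EQ-5D-5L, Lachman) the baseline is a post-injury value, taken in an earlier window in study 1 than in study 2. If the knee is temporarily worse in the earlier window, DIS patients have further to recover and show a larger change even when both groups are the same at 24 months.

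**Working it through.** **The plan's own figure.** Inputs from Sample size: difference 13, SD 13, alpha 0.025, power 80%, dropout 10%. A two-sided t-test gives n = 20.3, rounded up to 21 per arm (power 81.5%), and 21/0.9 = 23.3, rounded up to 24. Both stated figures reproduce. No figure is stated for the secondary outcomes; 21 per arm is used below only for scale.

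**Precision within a randomised study.** Assume equal SD s at baseline and 24 months and correlation ρ. The documents give neither, so a range is shown.

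- Variance on the change score: 2(1−ρ)s²
- Variance with baseline as covariate: (1−ρ²)s²
- Ratio, adjusted to change: (1+ρ)/2

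| ρ | 2(1−ρ) | 1−ρ² | Ratio | Reduction | 21 per arm on change is worth |
|---|---|---|---|---|---|
| 0.2 | 1.60 | 0.96 | 0.60 | 40% | 12.60 |
| 0.5 | 1.00 | 0.75 | 0.75 | 25% | 15.75 |
| 0.7 | 0.60 | 0.51 | 0.85 | 15% | 17.85 |
| 0.9 | 0.20 | 0.19 | 0.95 | 5% | 19.95 |

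Below ρ = 0.5, 2(1−ρ) exceeds 1, so the change score is noisier than ignoring the baseline altogether. Estimating the slope in 42 patients costs about (42−3)/(42−4) = 1.026, or 2.6% in variance, which takes back roughly half of the gain at ρ = 0.9. Simulation (20,000 runs, 21 per arm) gave standard errors for change and adjusted of 0.392 and 0.307 at ρ = 0.2, and 0.308 and 0.270 at ρ = 0.5. The variance ratios are 0.61 and 0.77, as expected once that cost is included.

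Approximate power for a 0.8 SD difference (two-sided 0.05, slope cost ignored), change versus adjusted: 52% v 73% at ρ = 0.2, 72% v 83% at 0.5, 90% v 94% at 0.7.

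**Bias in an unanchored DIS versus reconstruction contrast.** Suppose the study 1 baseline is worse by d SD, the gap is transient, and there is no true difference at 24 months. The expected contrast is d on change, ρd with baseline as covariate, and 0 on the 24-month value. Simulated false-positive rates (two-sided 0.05, 21 per arm), with d and ρ assumed:

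| d | ρ | Change | Baseline-adjusted | 24-month value |
|---|---|---|---|---|
| 0.25 | 0.3 | 10.1% | 5.8% | about 5% |
| 0.25 | 0.5 | 12.5% | 7.3% | about 5% |
| 0.5 | 0.3 | 27.1% | 7.7% | about 5% |
| 0.5 | 0.5 | 34.9% | 13.9% | about 5% |

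Adding the baseline therefore shrinks this bias but does not remove it.

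**Outcome list against Table 1.**

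| Outcome | Pre-operative value | Week 104 value |
|---|---|---|
| VAS pain, knee function, EQ-5D-5L, Lachman | post-rupture | yes |
| Tegner, Lysholm | pre-rupture | yes |
| VAS satisfaction | none | yes |
| Hop and drop-jump tests | none | none |
| Isokinetic, proprioceptive | post-rupture | none |

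Only the first row is exposed to the recovery-stage bias. For the last three rows the stated change to 24 months cannot be computed.

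**The case against.** **Change may be shorthand.** The primary endpoint is also described as a change in IKDC, yet it is modelled as the 6-month value on treatment and baseline. If the secondary sentence means the same, nothing is lost: regressing change on treatment plus baseline gives the same treatment estimate as regressing the follow-up value on both. This stands as a possibility. But the secondary sentence makes change the dependent variable, the covariate list omits the outcome's baseline, and the one-covariate ANCOVA is not tied to it. The mixed model is an additional analysis and does not replace the regression.

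**The comparison is already caveated.** The protocol calls DIS versus reconstruction non-randomised. This stands, but a caveat does not remove a gap built into the endpoint, and no listed confounder represents it.

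**The direction is not documented.** A reader might infer that all secondary outcomes favour DIS by construction. The documents do not support that. Tegner and Lysholm have pre-rupture baselines. No baseline values by window are given. The Study design remark concerns knee function, and says nothing of laxity on the Lachman test. Patients who do not reach 90° of flexion before surgery are excluded from both studies, which narrows any gap in function.

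**The randomised comparisons are not biased.** Correct: there the issue is efficiency only, and the protocol makes no power claim for secondary outcomes that would be contradicted.

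**Anchoring would cancel the gap.** Also correct: in a contrast through the two IBLA arms with a study term, a study-wide baseline gap drops out even on change. The protocol does not describe such a model, and it has a price (see the fix).

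**Conclusion.** The point holds in limited form and for secondary outcomes only; the primary analysis is untouched.

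In the two randomised comparisons the stated analysis is valid but less precise than the protocol's own IKDC model. The variance saving from adjustment runs from 40% at ρ = 0.2 to 5% at ρ = 0.9, given equal SDs and an assumed ρ. Equal SDs may not hold between an early post-injury baseline and 24 months.

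For DIS versus reconstruction on VAS pain, knee function, EQ-5D-5L and Lachman, change from baseline may be biased one for one by a transient baseline gap. The direction is probably towards DIS for function, pain and EQ-5D-5L and is open for Lachman. The size cannot be stated, because the documents give no baseline values by window. The preference for 24-month values rests on the gap being transient; if it reflected lasting differences between the patients of the two studies, those values would be confounded too, which is why the non-randomised caveat must remain.

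Separately, and without any assumption, the outcome list and Table 1 do not agree.

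**What to change.** 1. Within each randomised study, regress the 24-month value on treatment with the outcome's own baseline as covariate, as for IKDC.
2. For DIS versus reconstruction on the four outcomes with a post-rupture baseline, do not interpret change from baseline. Compare the 24-month values and keep the non-randomised caveat.
3. Optionally add, as supportive, a contrast through the IBLA arms with a study term. State its price: it uses four arm means instead of two, so the variance goes from 2s²/n to 4s²/n, roughly double, and it assumes that relative effects do not depend on timing.
4. Reconcile the outcome list with Table 1. VAS satisfaction and the hop and drop-jump tests have no pre-operative value and can only be compared as follow-up values. The hop, drop-jump, isokinetic and proprioceptive measures need a time point at which they are taken (week 52 is the last) or an added assessment.

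Items 1 and 2 cost wording only and use data already collected. Item 3 costs precision, so it should not replace item 2. Item 4 costs wording unless assessments are added.

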#### Secondary objectives

To assess whether DIS and IBLA offer an improvement in quality of life, patient satisfaction and functioning of the patient compared to conventional ACL reconstruction.To assess whether DIS and IBLA result in a shorter recovery period compared to conventional ACL reconstruction in terms of the mobilization period with crutches after the surgery, and return to work and sports period.To assess whether there is a difference between DIS and IBLA versus conventional ACL reconstruction in terms of pain and complications during and after surgery.To assess whether there is a difference between DIS and IBLA versus conventional ACL reconstruction in terms of ACL re-ruptures/failures.To determine the economic benefit of the two alternative techniques DIS and IBLA in comparison to the conventional ACL reconstruction for treating an acute ACL rupture.For all of these objectives also the mutual comparison between DIS and IBLA will be considered.

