#### Analysis of safety endpoints

The number of patients with SAEs will be reported per treatment arm.The proportion of patients having complications will be compared between the different treatments using a Chi-square test.

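### Confounder correction is promised for all analyses, but the plain log-rank and chi-square tests named for recovery times, MRI and complications cannot deliver it, which matters for the non-randomized DIS versus reconstruction contrast

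*Protocol article*

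**What the plan says.** Under Analysis of the secondary outcomes, the protocol article fixes the method for the recovery times: "A survival analysis with log-rank test will be used to compare the time to return to work and time to return to sports". Crutch use follows: "The time from the surgery until the patient is mobile without crutches will be analysed in the same way". MRI morphology and signal are to be "compared between the different treatments using a Chi-square test at the different time points". Under Analysis of safety endpoints: "The proportion of patients having complications will be compared between the different treatments using a Chi-square test".

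The closing paragraph of the secondary-outcomes section makes a general promise: "In all the analyses there will be appropriately corrected for possible confounders (age, gender, working category, Tegner score of more than 7"), and singles out one contrast: "especially in the analysis where the ACL reconstruction arm is compared to the DIS arm as this is a non-randomized comparison". It then says how: "As the sample size is small mainly ANCOVA models where only one covariate is added will be explored". It adds that the covariates cannot all be combined and that conclusions on the non-randomized comparison will be worded with care.

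These outcomes belong to the DIS versus reconstruction question. The Secondary objectives include "To assess whether DIS and IBLA result in a shorter recovery period compared to conventional ACL reconstruction", measured by crutch use and return to work and sports, and a further objective covers complications. For the primary outcome, by contrast, DIS versus reconstruction has its own adjusted linear regression.

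**The concern.** A plain log-rank test and a plain chi-square test compare groups and hold no covariate. ANCOVA does hold one, but it is a model for continuous outcomes, not for censored times, MRI grades or the occurrence of a complication. So for five outcomes (return to work, return to sports, crutches, MRI, complications) no method named in the article can carry out the correction that the article promises.

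For DIS versus IBLA (study 1) and IBLA versus reconstruction (study 2) randomization covers this, and little is lost. DIS versus reconstruction compares an arm of one study with an arm of the other. An imbalance in job type or activity level would then appear as faster or slower recovery after DIS. Working category, which the plan itself lists as a confounder, bears most directly on return to work. An analyst who follows the named tests misses the promise. One who follows the promise must pick a model that the article does not name.

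**Working it through.** **Methods set side by side (protocol article, Statistical analyses)**

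| Outcome | Named method | Can it hold a covariate as named? |
|---|---|---|
| IKDC, DIS versus reconstruction | linear regression | yes |
| Other continuous outcomes | linear regression, mixed model | yes |
| Return to work, return to sports, crutches | log-rank | no |
| MRI | chi-square | no |
| Complications | chi-square | no |

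No Cox model, stratified log-rank test, logistic model or Cochran-Mantel-Haenszel test appears anywhere in the article.

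**Arm size.** The Sample size section gives 21 per arm, then 24. With a two-sided t-test, alpha 0.025, difference 13 and SD 13, 20 per arm gives 79.3% power and 21 gives 81.5%; 21 / 0.9 = 23.3, so 24. The figure reproduces. I use 24 per arm below.

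**Illustration for the log-rank test (assumed inputs).** The document gives no imbalance and no job effect. Assume no treatment effect, one binary job class, and a return rate in that class equal to r times the rate in the rest. With class shares p1 and p2, the initial rate ratio between arms is

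R = (p1·r + 1 − p1) / (p2·r + 1 − p2).

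If nearly all 48 patients have the event, SE(ln R) is about √(4/48) = 0.289. With d = |ln R| / 0.289, the rejection rate at nominal 5% is Φ(−1.96 + d) + Φ(−1.96 − d).

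- 50% v 25%, r = 0.4: R = 0.70/0.85 = 0.82, d = 0.67, rejection 10%.
- 60% v 30%, r = 0.4: R = 0.64/0.82 = 0.78, d = 0.86, rejection 14%.
- 50% v 30%, r = 0.5: R = 0.75/0.85 = 0.88, d = 0.43, rejection 7%.
- 40% v 30%, r = 0.5: R = 0.80/0.85 = 0.94, d = 0.21, rejection 5.5%.

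Simulation (24 per arm, exponential times, censoring at 104 weeks) agrees. The first three cases give about 10% to 12%, 12% to 14% and 7% to 8.5%. The lower end holds the class split fixed in each arm; the upper end draws it at random. The unadjusted hazard ratios are about 0.81, 0.78 and 0.88. The 40% v 30% case gives about 6%, the same as balanced classes. In the first case, Cox regression with the job class gives a hazard ratio of 1.00 and 6%; stratified log-rank tests give 5% to 6%.

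**Illustration for the chi-square test (assumed inputs).** Event risk 40% with the confounder and 15% without, no treatment effect.

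- 65% v 35%: expected risks are 0.65·0.40 + 0.35·0.15 = 31.25% and 0.35·0.40 + 0.65·0.15 = 23.75%. Simulated rejection is 9% plain and 5% with Cochran-Mantel-Haenszel.
- 70% v 30%: expected risks are 32.5% and 22.5%. Simulated rejection is 13% plain and 5% with Cochran-Mantel-Haenszel.

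**The case against.** The strongest reply is that the plan states the right intention. A reader might infer that DIS versus reconstruction will be analysed without adjustment on these outcomes. The document does not support that: it says the opposite, and most firmly for this contrast. A reader might also infer that the two statements can never be reconciled. That goes too far as well. Stratified log-rank and Cochran-Mantel-Haenszel tests are adjusted forms of the named tests; working category, gender and Tegner above 7 are categorical; and the one-covariate approach suits stratification. A condensed article may leave such detail to the analysis plan.

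Most of this stands, and it limits the point to the named methods. It does not remove the point, because the article does not leave the method open. It names specific tests whose plain forms cannot do what it promises, and it names no adjusted form for these outcomes.

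Further limits also stand:

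- The gap does not cover every categorical outcome. Failure is a secondary endpoint with no test named.
- Complications come under a later safety heading, so whether the promise reaches them is partly a matter of reading.
- The plan says that conclusions on the non-randomized comparison will be carefully stated. That sentence, however, concerns the inability to combine covariates, not outcomes whose named test holds none.
- Putting all four confounders in one model would conflict with the plan's own small-sample limit.

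**Conclusion.** The point holds in this form: for return to work, return to sports, crutches, MRI and complications, no method named in the article can deliver the promised correction. Run as named, the tests leave DIS versus reconstruction open to confounding. The two randomized comparisons are largely unaffected, and so is the sample size.

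The size is conditional. With a 20 to 30 point imbalance in a job class that returns at 0.4 to 0.5 of the usual rate, log-rank false positives are about 7% to 14%, against about 6% when balanced. With a 10-point imbalance there is little effect. All of these imbalances and effects are assumptions; none comes from the document.

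Covariate adjustment would not make this contrast equivalent to a randomized one. The surgery window (0–4 v 5–12 weeks) coincides with it. For MRI so does the scanner: 1.5 T for DIS, 3 T for the other arms.

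**What to change.** For DIS versus reconstruction:

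- **Return to work, return to sports, crutches:** replace the plain log-rank test by Cox regression, or by a log-rank test stratified by one covariate named in advance for each outcome (for example working category for return to work). Give a hazard ratio with its confidence interval.
- **Complications and MRI:** replace the plain chi-square tests by logistic regression (complications) and ordinal regression (MRI grades), penalised if events are sparse, or by Cochran-Mantel-Haenszel, again with one pre-named covariate. Give estimates with confidence intervals.
- **Too few events to adjust:** report the contrast descriptively, without a p-value.

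Reword the promise of correction in all analyses so that unadjusted log-rank and chi-square tests may stand for DIS versus IBLA in study 1 and IBLA versus reconstruction in study 2. State that adjustment cannot remove the surgery-window difference or, for MRI, the scanner difference.

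The cost is wording and a few extra models; the confounders are already listed and no more patients are needed. The downside is reliance on proportional hazards or proportional odds, and slightly wider intervals.

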### Sample size

The primary outcome is change in IKDC score from baseline (pre-rupture) to 6 months post-operatively. A difference in IKDC change score of 13 points between the treatment arms is considered clinically meaningful as described by Irrgang et al. and Collins et al. [46, 47]. In order to detect an effect of 13 IKDC points with 80% statistical power between any of the two treatment arms using an independent samples t-test in which alpha is 0.025 (alpha corrected for the fact that per study data set 2 tests will be performed), assuming a standard deviation of 13 on the change in IKDC score per arm (SD found in pilot study), we need 21 patients per arm. Taking into account a drop out of 10%, we need 24 patients per arm or 48 patients in total which have to be randomized.

In study 1, 24 patients per arm (DIS and IBLA) will be included and in study 2, 24 patients per arm (IBLA and ACL reconstruction) will be included. The total number of patients to be included is 96. We expect that 50% of the patients will be included in Antwerp University Hospital and 50% in University Hospital Brussels. We also expect that the total number of addressed patients will range from 96 to 106, since we expect that about 10% of the patients will not have a repairable, proximal ACL rupture. They will not be eligible (any more) after the intra-operative confirmation and these patients (exploratory group) will not contribute the number of 96 patients needed for inclusion.

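### Pre-rupture Tegner score is adjusted for only as above or not above 7; entering the score itself is a free improvement wherever a model includes Tegner

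*Protocol article*

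**What the plan says.** The last paragraph of Analysis of the secondary outcomes lists the covariates to be corrected for in all analyses: "possible confounders (age, gender, working category, Tegner score of more than 7". It stresses the comparison of DIS with reconstruction, which is not randomised. Two limits follow: "As the sample size is small mainly ANCOVA models where only one covariate is added will be explored", and "any conclusion for the non-randomized comparison will be carefully stated".

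For the primary outcome, every model has "IKDC at 6 months as outcome and treatment, and IKDC at baseline as predictors". The model for DIS versus reconstruction adds: "As this is a non-randomized comparison this model will correct for possible confounders like age, gender and working category". Tegner is not named there, but the list is given by way of example.

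Table 1 under Study procedures records, before surgery, "Pre-rupture: Tegner score, Lysholm score and IKDC score". Exclusion criteria removes Tegner scores below 3, so enrolled patients score 3 or more. Analysis of the secondary outcomes also lists Tegner among the continuous outcomes to be analysed by linear regression and a mixed model.

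**The concern.** The natural reading of the covariate list is a yes/no term. It treats a patient who scored 3 before injury like one who scored 7, and one who scored 8 like one who scored 10. Yet the same score is treated as continuous when it is an outcome.

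Coding matters most for DIS versus reconstruction. Patients enter study 1 or study 2 according to when they present, so covariate adjustment is the main protection against bias in that comparison. The protocol itself names activity level as a possible confounder. Differences in Tegner within 3–7, or above 7, are not corrected by the two-level term. The sample is too small for many covariates, which makes it more important that the one added carries its full information. A numeric term costs one degree of freedom, the same as the cut.

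**Working it through.** **The plan's own figure.** Sample size states "A difference in IKDC change score of 13 points between the treatment arms is considered clinically meaningful", "assuming a standard deviation of 13 on the change in IKDC score per arm", alpha 0.025 and power 80%. A two-sided t-test at a standardised difference of 13/13 = 1 needs 20.3, so 21 per arm; 21/0.9 = 23.3, so 24 with 10% dropout. The stated 21 and 24 reproduce and are not affected by this point. The protocol gives no Tegner distribution, no slope of IKDC on Tegner and no expected difference between the studies, so everything below rests on assumptions.

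**Formula.** Suppose Tegner is normal with standard deviation s, its effect is linear, and the groups differ by a small shift d. Let p be the share above 7, c the matching standard normal cut, and φ the normal density.
- The shift changes the share above 7 by φ(c)·d/s.
- The slope of Tegner on the indicator is s·φ(c)/(p(1−p)).
- Adjusting for the indicator therefore removes d·φ(c)²/(p(1−p)).
- Share of the confounding left = 1 − φ(c)²/(p(1−p)).

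| Share above 7 | φ(c)² | p(1−p) | Share left |
|---|---|---|---|
| 0.10 | 0.0308 | 0.09 | 66% |
| 0.20 | 0.0784 | 0.16 | 51% |
| 0.30 | 0.1209 | 0.21 | 42% |
| 0.50 | 0.1592 | 0.25 | 36% |

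**Whole-number scores 3–10** (discretised normal, linear effect). With 11–69% of patients above 7, 30–56% is left; with 5–7% above 7, 71–74% is left. Uniform scores give 29%.

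**Finite shifts between groups** (population regression of the outcome on group and the cut, linear effect):

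| Means | SD | Shares above 7 | Share left |
|---|---|---|---|
| 7 and 8 | 1.5 | 0.36, 0.61 | 32% |
| 6.5 and 7.5 | 1.5 | 0.25, 0.49 | 36% |
| 6 and 7 | 2 | 0.23, 0.38 | 39% |
| 6 and 7 | 1.5 | 0.16, 0.36 | 44% |
| 6 and 6.5 | 1.5 | 0.16, 0.25 | 48% |
| 5 and 6 | 1.5 | 0.05, 0.16 | 64% |
| 5.5 and 6.5 | 1 | 0.02, 0.16 | 72% |

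The two approaches together give about 30–70%.

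**Where the range fails.** If the outcome changes only at the step above 7, the cut leaves 0%. If the groups differ only in the share above 7, it also leaves 0%. If they differ only below the cut, it leaves 100%.

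**The alternative coding.** With a linear effect, the numeric score leaves 0%, but that follows from the assumption. A fairer test gives the outcome a true step above 7 and uses the numeric score anyway. For the seven shifts in the table, between −9% and 3% is left. Under a whole-distribution shift the numeric term therefore loses little even when the cut is the right form. It is not always better: with a true step and groups that differ only in the share above 7 (20% against 40%; mean 6.5, SD 1.5 within the strata), the numeric term leaves 41% and the cut leaves none.

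**In IKDC points.** Bias left = share left × difference in Tegner × IKDC points per Tegner point. The last factor is unknown. For scale, with 60% left and a one-point difference, a bias of 2 IKDC points needs 2/0.6 = 3.3 IKDC points per Tegner point, or 3.3 × 7 = about 23 points between scores 3 and 10, beyond what baseline IKDC explains. The standard error of a comparison with 21 per arm is 13·√(2/21) = 4.0 points.

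**The case against.** A reader might infer that a third to more than half of any activity-level confounding is bound to stay in the DIS versus reconstruction comparison. The protocol does not support that. The share depends on a distribution, a shape of effect and a type of imbalance that it does not give, and it runs from 0% to 100%. Whether activity level confounds the comparison at all is not shown. The calculations also leave out baseline IKDC, which is in every primary model and may absorb part of the difference. The scale calculation suggests that the bias could be small beside the standard error. All of this stands.

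Three further points limit the reach of the change, and they also stand.
- Under the one-covariate approach, a model that adds age, gender or working category has no Tegner term in any coding. This may matter more than the coding does.
- Return to work, return to sport and time on crutches are compared by log-rank test, which has no covariate term, so no gain can be claimed there.
- The protocol already promises caution about the non-randomised comparison. The small sample is its reason for limiting the number of covariates, and it does not offer that as the reason for the cut.

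It can also be said that coding belongs in a fuller document. That would hold if the article were silent, but it states the cut.

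**Conclusion.** The point holds in a conditional and modest form. The protocol fixes a coarse coding of a score that it collects in full and elsewhere treats as continuous. With a roughly linear effect and a whole-distribution shift between groups, about 30–70% of any confounding by Tegner would be left in models that use the cut. The low end applies when about half the patients score above 7, the high end when few do. The effect in IKDC points cannot be derived from the protocol, and no bias of a given size is established. Nothing in the protocol points to a threshold at 7, so the numeric score is the better default. This is a free or cheap improvement, not a flaw that undermines the trial's conclusions.

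**What to change.** In the covariate list that closes Analysis of the secondary outcomes, replace the cut with the pre-rupture Tegner score as a numeric covariate. Use the same coding in any regression or ANCOVA model under Analysis of the primary outcome that includes Tegner. Keep the cut at 7 for description, or as a sensitivity analysis with its reason stated if a threshold was intended. Leave the caution on the non-randomised comparison as it is.

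The cost is a change of wording: no new data, no extra patients and the same one degree of freedom. The small downside is an assumption of approximate linearity in an ordinal score, which the sensitivity analysis with the cut would help to check.
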